## Abstract

**Background and objectives:**

Intermittent theta-burst stimulation (iTBS) is a patterned form of excitatory transcranial magnetic stimulation that has yielded encouraging results as an adjunctive therapeutic option to alleviate the emergence of clinical deficits in Parkinson’s disease (PD) patients. Although it has been demonstrated that iTBS influences dopamine-dependent corticostriatal plasticity, little research has examined the neurobiological mechanisms underlying iTBS-induced clinical enhancement. Here, our primary goal is to verify whether iTBS bilaterally delivered over the primary motor cortex (M1) is effective as an add-on treatment at reducing scores for both motor functional impairment and nonmotor symptoms in PD. We hypothesize that these clinical improvements following bilateral M1-iTBS could be driven by endogenous dopamine release, which may rebalance cortical excitability and restore compensatory striatal volume changes, resulting in increased striato-cortico-cerebellar functional connectivity and positively impacting neuroglia and neuroplasticity.

**Methods:**

A total of 24 PD patients will be assessed in a randomized, double-blind, sham-controlled crossover study involving the application of iTBS over the bilateral M1 (M1 iTBS). Patients on medication will be randomly assigned to receive real iTBS or control (sham) stimulation and will undergo 5 consecutive sessions (5 days) of iTBS over the bilateral M1 separated by a 3-month washout period. Motor evaluation will be performed at different follow-up visits along with a comprehensive neurocognitive assessment; evaluation of M1 excitability; combined structural magnetic resonance imaging (MRI), resting-state electroencephalography and functional MRI; and serum biomarker quantification of neuroaxonal damage, astrocytic reactivity, and neural plasticity prior to and after iTBS.

**Discussion:**

The findings of this study will help to clarify the efficiency of M1 iTBS for the treatment of PD and further provide specific neurobiological insights into improvements in motor and nonmotor symptoms in these patients. This novel project aims to yield more detailed structural and functional brain evaluations than previous studies while using a noninvasive approach, with the potential to identify prognostic neuroprotective biomarkers and elucidate the structural and functional mechanisms of M1 iTBS-induced plasticity in the cortico-basal ganglia circuitry. Our approach may significantly optimize neuromodulation paradigms to ensure state-of-the-art and scalable rehabilitative treatment to alleviate motor and nonmotor symptoms of PD.

## Introduction

Parkinson’s disease (PD) is increasing more rapidly than that of other neurological conditions, with the disease affecting mostly middle-aged persons (Dorsey et al., 2018). Aside from the inherent complexity of the pathophysiology itself, the annually increasing prevalence of PD poses a further challenge for public health systems in aging societies (Rodríguez-Blázquez et al., 2015), which must offer treatments that mitigate the medical, social, and personal impacts of this disease as well as identify clinical markers of treatment effectiveness. Clinically, PD is characterized by the presence of heterogeneous symptoms, predominantly consisting of typical motor symptoms, such as bradykinesia, tremor, rigidity, gait disorder, and postural instability, which have a significant clinical impact on patients and relatives (Weiner, 2006; Moustafa et al., 2016). Nonmotor features, such as cognitive impairment, sleep disorders, and mood and affect changes, also occur frequently, with a considerable impact on disability and health-related quality of life (Chaudhuri et al., 2006; Schapira et al., 2017; Macías-García et al., 2022). Pathologically, the loss of dopaminergic neurons and decreased striatal dopamine levels have been proposed as the mechanisms behind motor deficits in PD (Rosin et al., 2007). This denervation induces significant changes in synaptic functioning, increases maladaptive neural activity along cortico-striatal-pallido-thalamic-cortical circuits (Kish et al., 1988; Salenius et al., 2002; Herz et al., 2014; Weiss et al., 2015), and alters glucose metabolism and blood flow in the brain (Obeso et al., 2008; Nandhagopal et al., 2011; Stoessl et al., 2014). The pathology also features nonspecific alterations in gray matter (GM) and white matter (WM) at structural and functional levels in the BG-thalamo-cortical circuit (Lewis et al., 2016; Sterling et al., 2016; Filippi et al., 2020), resulting in progressive atrophy in various brain regions from onset to the intermediate phases (Filippi et al., 2020; Sarasso et al., 2021).

Dopamine-based treatments such as levodopa are commonly used to alleviate motor symptoms PD; the principal drawbacks of these replacement treatments are the limited time window for their use and the fact that they can lead to dyskinesias, motor fluctuations, and cognitive problems (Lang and Espay, 2018). Alternative therapies, such as noninvasive brain stimulation and repetitive transcranial magnetic stimulation (rTMS), are being explored for the treatment of motor and nonmotor symptoms in PD patients. Current evidence suggests that while low-frequency rTMS (≤1 Hz) has an inhibitory impact (Chen et al., 1997), high-frequency rTMS (≥ 5 Hz) induces excitability in the cortex (Pascual-Leone et al., 1994; Kobayashi and Pascual-Leone, 2003). Recently, theta-burst stimulation (TBS), an rTMS pattern involving bursts of high-frequency stimulation that mimics neural oscillatory patterns, has been shown to increase or decrease cortical excitability depending on the presence of an intertrain interval, i.e., whether the protocol is continuous (cTBS) or intermittent (iTBS; Di Lazzaro et al., 2005; Huang et al., 2005; Gamboa et al., 2011). The evaluation of this technique as a potential therapeutic modality with promising outcomes in neurorehabilitation in a variety of neurological and neuropsychiatric disorders has been prompted by the finding that the modulatory effects of both rTMS and TBS induce neuroplasticity that lasts beyond the stimulation period (Huang et al., 2017; Kricheldorff et al., 2022). Current evidence suggests that the application of iTBS and cTBS patterns to the motor cortex can facilitate or depress corticospinal excitability, respectively, and induce synaptic plasticity, as revealed in experimental models of PD (Chen and Udupa, 2009; Ghiglieri et al., 2012; Natale et al., 2021) and multiple studies on cortical plasticity in humans, in which the effect lasted from minutes to hours after administration (Di Lazzaro et al., 2005; Huang et al., 2005, 2017; Wischnewski and Schutter, 2015). Thus, the majority of PD studies suggest that cTBS over the supplementary motor area (SMA) has strong potential to enhance motor function and that iTBS over the motor primary area (M1) or the dorsolateral prefrontal cortex may improve specific aspects of motor performance, gait, and nonmotor symptoms in PD (Cheng et al., 2022). Nevertheless, despite the undeniable advantages of TBS over conventional TMS, the conclusions of these studies have some inconsistencies, particularly in terms of the duration and variability of the clinical effects in this patient population, the target of stimulation, and the role of dopaminergic medication use.

Yet, the potential advantages that iTBS brings to PD patients remain an open question, particularly regarding the degree to which iTBS-induced excitability and plasticity chances are confined to the cortical level, influencing GABAergic and fast-spiking interneurons and modulating inhibitory control of pyramidal cell output activity (Di Lazzaro et al., 2005; Benali et al., 2011), or whether these changes may be accompanied by changes at subcortical and striatal locations (Ghiglieri et al., 2012). On this topic, preclinical and human experiments have shown that iTBS enhances spontaneous neuronal firing and induces long-term potentiation (LTP)-like changes in M1 (Huang et al., 2005; Ziemann and Siebner, 2008; Wischnewski and Schutter, 2015), which might directly or indirectly facilitate the modulation of striatal dopamine release (Strafella et al., 2003, 2005; Ohnishi et al., 2004) and other nondopaminergic pathways (Aceves-Serrano et al., 2022), supporting the idea that a rescue of corticostriatal plasticity and a recovery of corticostriatal long-term depression (LTD), which becomes impaired in PD, may underlie the recovery of motor control in PD patients after M1-iTBS (Cacace et al., 2017; Natale et al., 2021).

At present, more research effort is needed to develop functional and structural biomarkers that determine the efficacy of iTBS-related clinical interventions and to characterize small changes in motor and nonmotor symptoms; many questions remain regarding the pattern of brain structural changes following TBS in PD patients (Huang et al., 2017; Ji et al., 2021). Likewise, more work is needed to characterize the underlying neural mechanisms by which TBS influences macro- and microstructural damage and whether these types of damage represent different neurodegenerative progresses. Regarding these matters, a growing body of research has shown that rTMS and TBS may modulate or induce neurological changes involving inflammation, neuroprotection and neurodegeneration, both during and after treatment (Bashir et al., 2022), but the precise neurobiological mechanism underlying the potential neurorestorative effects of iTBS in patients with PD is still not fully understood (Suppa et al., 2016; Natale et al., 2021). Furthermore, although the direct involvement of cortico-BG pathways in motor symptom alleviation in PD patients after TBS therapy has been suggested (Cárdenas-Morales et al., 2010; Chen et al., 2022), it remains unclear how structural and functional brain changes are ultimately associated with serum biomarkers of neurodegeneration and neuroplasticity and how they contribute to clinical improvement.

To validate the therapeutic effectiveness of iTBS as an adjunct to standard dopaminergic therapy on motor and nonmotor symptoms in PD patients on medication, we designed this randomized, double-blind, sham-controlled crossover study protocol in which iTBS is applied over the bilateral M1. Additionally, given that few studies have explored the neuronal correlates of the clinical and/or neuroprotective effects of iTBS, we will also investigate the potential neurobiological mechanisms of their therapeutic actions by assessing the relationships of dynamic brain changes (assessed by structural magnetic resonance imaging [MRI] and resting-state electroencephalography [EEG] and functional MRI [fMRI] data) with blood markers of neurodegeneration and neuroplasticity as well as possible clinical benefits.

Therefore, a major strength of this study will be its examination of the short-term motor and nonmotor impacts of bilateral M1-iTBS in patients with PD by exploiting the current trends in neuroimaging and serum biomarker testing to develop a multimodal architecture that characterizes brain structural and functional integrity in PD patients and its likely relationship with symptom dimensions.

## Methods

### Description of the protocol study design

We designed a single-center, randomized, double-blind, sham-controlled, crossover protocol study on patients with PD; these patients will be recruited at the Puerta del Mar University Hospital of Cadiz. The aim is to investigate the clinical efficacy of bilateral M1 iTBS (administered in 5 sessions) as well as its association with neuropsychological and cortical excitability changes, brain imaging data, and serum biomarkers.

### Recruitment and sample size

The recruitment period will last approximately one and a half years. During this time, we plan to enroll 24 PD patients who meet the inclusion and exclusion criteria. Recruitment will be entirely managed by neurologists from the Movement Disorders Unit at the Puerta del Mar University Hospital. Every candidate patient will undergo a clinical review by a neurologist specializing in movement disorders, who will assess the suitability of each patient for inclusion in this study.

The inclusion criteria for patients will be as follows: (i) diagnosed with PD according to the United Kingdom Parkinson’s Disease Society Brain Bank diagnostic criteria (UK PDSBB; Gibb and Lees, 1988); (ii) disease duration of at least 5 years to reduce the risk of including levodopa-responsive atypical Parkinsonism patients (Lang et al., 2006; Tolosa et al., 2006; Mestre et al., 2014); (iii) disease symptomatology in the ON medication state at a Hoehn y Yahr (H&Y) scale of II–III; (iv) clinical and therapeutic stability in the last 2 months previous to the recruitment period; and (v) aged 45–75 years.

The exclusion criteria will be as follows: (i) lack of a PD diagnosis that meets the UK PDSBB diagnostic criteria; (ii) presence of a serious systemic disease; (iii) presence of severe or moderate cognitive impairment comparable to dementia as indicated by a Mini-Mental Parkinson (MMP) score of ≤24; (iv) any incapacitating psychiatric or other clinical condition that might affect the correct performance of this protocol, such as any dystonia and/or dyskinesia; (v) receipt of amantadine within the previous 60 days; and (vi) any sign of atypical parkinsonism, neurological comorbidities, or history of cranioencephalic traumatism or epilepsy or any other contraindication to neurostimulation with TMS (e.g., magnetic intracranial implant, cardiac pacemaker).

The few TMS or TBS studies using a crossover design (Eggers et al., 2010; Maruo et al., 2013; Bologna et al., 2015; Kim et al., 2015; Vanbellingen et al., 2016; Yokoe et al., 2018; Hill et al., 2020; Brugger et al., 2021) have demonstrated the favorable efficacy of high-frequency rTMS over the M1 on motor symptoms in PD (compared to sham stimulation). The necessary sample size was calculated based on the primary endpoint, i.e., the motor clinical changes as assessed by the UPDRS-III score. Considering these findings and the statistical parameters needed to detect a treatment difference for a 2 × 2 crossover study at a two-tailed *p* value of 0.05 and a power of 80%, the total sample size was calculated to be at least 21 subjects. With an assumed drop-out rate of approximately 20%, we estimated a final minimum sample size of 24 patients.

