Most previous studies have supported the clinical efficacy of cTBS over the SMA for improving motor function in individuals with PD in the OFF medication state, but the clinical effect and ultimate clinical importance of iTBS over the M1 remain unclear and controversial. Thus, while a single session of cTBS over the M1 did not have any motor or clinical effects in PD patients in the OFF medication state (Eggers et al., 2010), a study using a single session of iTBS over the M1 was promising for alleviating complications in PD patients in the ON medication state (Degardin et al., 2012). However, some disagreements regarding the application of excitatory or inhibitory TBS protocols and the recommended brain targets during the ON medication state still need to be clarified (Cheng et al., 2022).

There is broad consensus that TBS protocols, like other types of rTMS, may promote cortical plasticity that treats disease, improves health, and modifies brain activity. Moreover, evidence indicates that the after-effects of TBS protocols are due to underlying mechanisms of synaptic plasticity. Accordingly, LTP and LTD are thought to be the processes underlying the stimulation and suppression of MEPs by iTBS and cTBS protocols, respectively. In this regard, the restoration of post-TBS MEP amplitudes to their baseline levels is a neurophysiologic indicator of the clinical effectiveness and efficacy of the mechanisms underlying cortical plasticity (Oberman, 2010; Pascual-Leone et al., 2011).

However, it is important to note that LTP and LTD pertain to extremely specific neurophysiologic events at the level of individual synaptic connections, and the alterations induced by TBS are not always limited to specific individual synaptic terminals. It is more probable that many of the positive effects of TBS are the result of the secondary activation of glial cells, although there is limited information regarding the response of glial cells to these neuromodulation techniques (Cullen and Young, 2016), particularly in relation to iTBS-induced plasticity effects (Cacace et al., 2017). Moreover, knowledge about how intracortical structures, cortico-subcortical functional connectivity, and brain volume changes are involved in the modulatory effects of rTMS and TBS is still limited (Di Lazzaro and Rothwell, 2014; Peters et al., 2020; Jannati et al., 2023; Kirkovski et al., 2023).

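### The sample-size figures of 21 required, about 20% drop-out and 24 enrolled do not reconcile: 24 keeps 21 only if drop-out is at most 12.5%

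*Protocol article*

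**What the plan says.** All the sizing figures stand in the protocol article under Recruitment and sample size.

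- The sizing endpoint is "the motor clinical changes as assessed by the UPDRS-III score".
- The design sized for is a crossover of two treatments in two periods. Significance level and power are set "at a two-tailed *p* value of 0.05 and a power of 80"%.
- The result before any allowance for losses: "the total sample size was calculated to be at least 21 subjects".
- The allowance for losses: "With an assumed drop-out rate of approximately 20%, we estimated a final minimum sample size of 24 patients".
- The enrolment target, given earlier in the same section: "we plan to enroll 24 PD patients who meet the inclusion and exclusion criteria". The Abstract also gives 24.

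The same section introduces the calculation with a list of crossover studies said to "have demonstrated the favorable efficacy of high-frequency rTMS over the M1 on motor symptoms in PD (compared to sham stimulation"). The Discussion describes one study on that list, from 2010, as finding that "a single session of cTBS over the M1 did not have any motor or clinical effects in PD patients in the OFF medication state".

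**The concern.** The step from 21 to 24 is meant to leave enough patients for 80% power after about one in five is lost. An allowance of 3 patients on 21 looks too small for that.

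If it is too small, the trial does not have the stated power under its own drop-out assumption. The sample-size statement is what a reader uses to judge a non-significant primary result, so the power quoted there should be the power expected after the losses the authors themselves foresee.

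The question does not depend on detail that an article may leave to the full protocol. The three numbers are printed as a finished calculation, and no further detail could make all three agree.

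**Working it through.** **Inputs, all from Recruitment and sample size:** two-sided alpha 0.05; target power 80%; 2 × 2 crossover; requirement n = 21; drop-out d = 0.20; enrolment 24.

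**Not given:** the effect size and the within-patient SD. The 21 therefore cannot be reproduced and is taken as correct. This assumption matters only for the power figures in step 4.

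**Step 1. Try to reproduce 24.**
- Correct inflation, n/(1 − d): 21/0.80 = 26.25, so 27, or 28 if the two sequences are to be equal. Check: 27 × 0.80 = 21.6, whereas 26 × 0.80 = 20.8.
- Mistaken shortcut, n × (1 + d): 21 × 1.20 = 25.2, so 26.
- Starting from 21, neither gives 24.

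**Step 2. Does the word approximately cover the gap?**
- The largest loss that leaves 21 of 24 is 1 − 21/24 = 3/24 = 12.5%.
- At 15% drop-out the need is already 21/0.85 = 24.7, so 25.
- A rate of 12.5% is not a rounding of 20%.

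**Step 3. What 24 leaves at 20%.**
- 24 × 0.80 = 19.2, so about 19.
- If patients drop out independently, each with probability 0.20, the chance that at least 21 of 24 complete is 26% (binomial).

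**Step 4. Power at 19.** Let d_z be the treatment effect divided by the SD of the within-patient difference. Power is the probability that |T| exceeds the 97.5% point of the t distribution, where T is noncentral t with noncentrality d_z × √n. Degrees of freedom are n − 1 (paired) or n − 2 (crossover with a period term).

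First, d_z is solved so that n = 21 gives exactly 80%. Then it is solved for the other extreme, in which 20 patients almost reach 80% and 21 is the rounded-up integer.

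| Case | d_z | Power at 19 | Power at 20 | Power at 21 | Power at 24 |
|---|---|---|---|---|---|
| 21 gives exactly 80%, df n − 1 | 0.643 | 75.5% | 77.8% | 80.0% | 85.4% |
| 21 gives exactly 80%, df n − 2 | 0.645 | 75.4% | 77.8% | 80.0% | 85.5% |
| 21 gives exactly 80%, normal approximation | 0.611 | 76.0% | 78.1% | 80.0% | 85.0% |
| 21 rounded up from just above 20, df n − 1 | 0.660 | 77.7% | 80.0% | 82.1% | 87.2% |
| 21 rounded up from just above 20, df n − 2 | 0.662 | 77.7% | 80.0% | 82.1% | 87.3% |

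The normal row by hand: d_z = (1.960 + 0.842)/√21 = 0.611. At n = 19, 0.611 × √19 − 1.960 = 0.705, and the standard normal probability below 0.705 is 0.760.

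So 19 completers give about 75–78%. The effect detectable with 80% power at n = 19 is d_z = 0.680 (df n − 1) or 0.682 (df n − 2), against 0.643 or 0.645 at n = 21.

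**Step 5. The literature sentence.** Recruitment and sample size counts the 2010 cTBS study among those showing benefit of M1 stimulation over sham. The Discussion cites the same study for no motor or clinical effect. The two descriptions cannot both stand.

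**The case against.** The strongest defence is that the practical gap is small and conditional. Only 3 patients (4 with equal sequences) separate 24 from the figure needed. The cost is roughly 2 to 5 percentage points of power. The 20% loss is an assumption and may not occur: with no losses, 24 patients give about 85% or more. All of this stands, and it limits the weight of the point. It does not make the printed figures agree.

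Several stronger readings are tempting but are not supported:

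- **Power is 75%.** A reader might quote this as a fact. With no effect size or SD in the article, it holds only if 21 gives exactly 80%. Because 21 is a rounded-up integer, power at 19 could be as high as 77.7%.
- **No calculation could have produced 24.** This is true only when starting from 21. An unrounded requirement just above 20, multiplied by 1.2, comes to just above 24. That is still the wrong formula, and dividing by 0.80 would give just above 25, so 26. The error remains, but its origin may be innocent.
- **Every drop-out removes a full within-patient comparison.** Procedure and intervention schedules four post-treatment motor evaluations in each phase, so a patient lost after the first of these in Phase II has motor data under both conditions. Statistical analysis removes patients with missing outcomes initially, but also mentions last observation carried forward. The figure of 19 is therefore the expected number of full completers. It is also the usable number only if losses come before usable data exist under both conditions.
- **The null cTBS study fed into the 21.** The article lists eight studies and does not say which supplied the effect. The conflict with the Discussion is real, but it is a citation matter and no link to the calculation can be shown.
- **The missing effect size is itself a fault.** A journal article may leave it to the full protocol. Here it only limits how precisely the power can be stated.

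**Conclusion.** The concern holds in a limited form. A requirement of 21, drop-out of about 20% and enrolment of 24 are mutually inconsistent, and no other section repairs this. This part is plain arithmetic and needs no assumption: 27 (28 balanced) would be required, and 24 is consistent with at most 12.5% drop-out.

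The power consequence is conditional. It assumes that 21 is the right requirement for 80% power and that the 20% are lost before giving usable data under both conditions. On those terms about 19 patients remain, power is about 75–78% instead of 80%, and the detectable standardised within-patient effect is about 0.68 instead of about 0.64.

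A reader might infer that the design or the analysis is invalid. It is not; a stated number is wrong and the stated power is somewhat optimistic. The conflicting descriptions of the 2010 cTBS study are a minor wording matter and add no weight to the arithmetic.

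**What to change.** Restate the figures in Recruitment and sample size in one of two ways:

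1. Keep 24 and say that it allows 12.5% drop-out (3 of 24) while retaining 21; or
2. Keep 24 and 20%, and say that about 19 completers are expected, with about 75–78% power, conditional on the calculation behind 21. The full calculation will allow one figure in place of the range.

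Either costs the rewording of one paragraph; the second makes the stated power slightly less favourable. If the authors want 80% power at 20% drop-out to stand as written, the matching enrolment is 27 (28 balanced). That means 3 or 4 more patients in a trial that, according to Study protocol status, was already recruiting with thirteen enrolled, so it is more than a wording change.

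As a minor correction, make the list of favourable crossover studies agree with the Discussion, either by removing the 2010 cTBS study from the list or by describing its result there as the Discussion does.
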